### Study setting

Patients with a stable kidney allograft, more than 6 months after transplantation, without a history of T1DM or T2DM routinely undergo an OGTT at our outpatient department. All patients with a pathological OGTT (serum glucose levels ≥ 200 mg/d (11.1 mmol/L)) are classified as patients suffering from NODAT. 32 Patients eligible for the study are invited to the outpatient clinic and therapeutic options are discussed. Patients who are willing to take part in the study and have signed their informed consent form are randomized in a 1:1 ratio into study arm A (vildagliptin) or study arm B (placebo). The detailed study flow chart and an overview of study procedures are depicted in Figure 1 and 2, respectively.

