### Statistical analysis plan

The statistical analysis plan (SAP) provides full details regarding the analyses, the data display, and the algorithms to be used for data derivations. The SAP includes the definition of major and minor protocol deviations which will be identified by medically trained staff before the study closure. Safety and tolerability are analyzed descriptively. Safety analysis is performed on the ITT population.

The study sample will consist of 32 patients with newly diagnosed NODAT. For the primary endpoint analysis, we will assess the differences between treatment and control group in the 2 h glucose value obtained during an OGTT (75 g glucose) after 3 months of vildagliptin or placebo treatment. Based on a two-sided testing and a standard deviation of 20% in relative changes of 2 h OGTT glucose values, α = 0.05 and ß = 0.2, a sample size of 16 patients per group can detect a minimal difference in serum glucose level of 20 mg/dl at the 2 hour time point of the OGTT when comparing baseline levels to levels on day 90. The "Last observation carried forward" (LOCF) method will be used for missing data.

Two different analysis sets are defined for safety and efficacy, respectively. The efficacy of vildagliptin is assessed in all subjects who received the study drug (at least one dose) and did not violate the protocol in a way that might affect the evaluation of the effect of the study drug(s) on the primary objective, i.e. without major protocol violations. The per-protocol set is employed in the analysis of efficacy variables. A sensitivity analysis will be performed for efficacy with the ITT population.

The safety analysis set includes subjects who were randomized and received at least one dose of the study drug (modified intention to treat). The safety set is employed in the analysis of tolerability and safety variables. Statistical analysis is performed with SPSS.

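### The sample-size sentence sets an SD in percent against a difference in mg/dl: as written, 16 per group has about 28% power for 20 mg/dl at a baseline of 200 mg/dl, not 80%

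*Protocol article*

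**What the plan says.** The sample-size justification is one sentence in the Statistical analysis plan section of the protocol article. Its assumptions are: "Based on a two-sided testing and a standard deviation of 20% in relative changes of 2 h OGTT glucose values, α = 0.05 and ß = 0.2". Its conclusion is that "a sample size of 16 patients per group can detect a minimal difference in serum glucose level of 20 mg/dl" at the 2 h point, for the comparison of baseline with day 90.

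The sentence before it defines the primary analysis as a comparison of treatment and control groups. The abstract describes the primary endpoint as the change in 2 h glucose from baseline to 3 months, compared between vildagliptin and placebo. Allocation is 1:1 (Study setting).

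The two scales are linked by the entry criterion. Table 1 requires a 2 h OGTT glucose of at least 200 mg/dl, and Study setting uses the same threshold to classify patients as having NODAT. The article gives neither an expected mean baseline nor an SD in mg/dl.

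**The concern.** A detectable difference means something only relative to an SD on the same scale. Here the number 20 appears twice with different units, and the entry criterion rules out that the two are equal: 20% of an eligible baseline is at least 40 mg/dl, twice the difference the sentence claims to detect.

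This sentence is the article's only justification for the size of the trial, and it concerns the primary endpoint. Taken at face value, it tells readers that the trial is sensitive to an effect about half as large as the smallest one its own SD allows it to detect with 80% power.

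**Working it through.** **Inputs.** From the Statistical analysis plan section: two-sided α = 0.05, power 0.80, SD of relative change 20%, difference 20 mg/dl, 16 per arm. From Table 1: baseline 2 h glucose at least 200 mg/dl. Mean baselines above 200 mg/dl are assumptions, shown as a range. The qualifying OGTT value is taken as the baseline.

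**1. Reproducing the plan's figure.** For two means, n per arm = 2(z₀.₉₇₅ + z₀.₈₀)² / d², where d is the difference divided by the SD.

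- With both 20s in the same unit, d = 20/20 = 1 and n = 2(1.960 + 0.842)² = 15.7, so 16 per arm.
- Power at 16 per arm is Φ(1 × √(16/2) − 1.960) = Φ(0.868) = 80.7% by the normal approximation.
- With the noncentral t distribution (30 degrees of freedom) it is 78.1%, and 17 per arm would be needed for 80%.

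So 16 follows from the usual normal formula at d = 1. The gap between 78% and 80% is only the difference between the two methods, not a further error.

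**2. The sentence as written.** At the lowest eligible baseline, SD = 0.20 × 200 = 40 mg/dl and d = 20/40 = 0.5.

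- Power at 16 per arm: Φ(0.5 × 2.828 − 1.960) = Φ(−0.546) = 29.3% (normal), or 27.8% (t).
- n per arm for 80% power: 15.7/0.25 = 62.8, so 63 (normal), or 64 (t).

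Power falls as the baseline rises, because the SD in mg/dl rises with it. Results for 16 per arm by t-test:

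| Mean baseline (mg/dl) | SD (mg/dl) | d for 20 mg/dl | Power for 20 mg/dl | Difference detectable with 80% power (mg/dl) |
|---|---|---|---|---|
| 200 (entry floor) | 40 | 0.50 | 27.8% | 41 |
| 220 (assumed) | 44 | 0.45 | 23.8% | 45 |
| 250 (assumed) | 50 | 0.40 | 19.5% | 51 |
| 300 (assumed) | 60 | 0.33 | 15.0% | 61 |

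The last column is 1.024 × SD, since 16 per arm detects 1.024 SD with 80% power by t-test. On the relative scale that is 1.024 × 20% = 20.5 percentage points. The normal approximation gives 19.8 points, or 39.6 mg/dl at 200.

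**3. What would make 20 mg/dl true.** The SD of change would have to be 20/1.024 = 19.5 mg/dl, which is 9.8% of a baseline of 200, about half the stated 20%. Put the other way, an SD of 20 mg/dl equals 20% only at a baseline of 100 mg/dl, far below the entry threshold.

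**4. Other tests.** At a baseline of 200 mg/dl, a one-sided two-group test has 39.6% power (t). A paired test within one arm of 16 has 46.5% (t). A paired test on all 32 patients pooled has 78.2% (t), but it discards the control group and does not match a statement made per group.

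**The case against.** The strongest reply is that this is a labelling slip. The figure of 16 is what the standard formula gives at d = 1, so if 20 percentage points was meant, the planned power is there and only the unit is wrong. That stands. A reader might infer from the 28% that the trial was sized wrongly or needs about 64 per arm. The documents do not support this, because they do not show that 20 mg/dl, rather than 20%, was the intended target.

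Nor do they settle which 20 carries the wrong unit. An SD of 20 mg/dl would also make the sentence consistent. The explicit reference to relative changes favours the percent reading but does not prove it.

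A reader might also take 28% as an upper limit. It is one only for an unadjusted comparison. The article names no test, and the separate SAP is not shown. If the 20% is an unadjusted SD and baseline correlates 0.5 to 0.7 with change (an assumption), adjustment raises power at baseline 200 to about 35% to 48%. Reaching 80% would take a correlation of about 0.87: √(1 − r²) = 0.5/1.024 = 0.488, so r² = 0.76. Adjustment therefore softens the figure but does not restore the claim.

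The reference to comparing baseline with day 90 might be read as a paired, within-arm test. It fits the change endpoint in the abstract and follows an explicit treatment-versus-control comparison, so it is not an error and should stay.

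Finally, it is tempting to say that a null result would be taken to exclude a benefit of 20 mg/dl. Nothing in the article says how a null result will be interpreted, so that remains a risk and not a finding.

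**Conclusion.** The sentence is wrong as written. With its own SD of 20% and an entry floor of 200 mg/dl, 16 per arm gives about 28% power for a 20 mg/dl difference at a baseline of 200 mg/dl, and less at higher baselines, against the stated 80%. The difference detectable with about 80% power is roughly 20 percentage points, which is at least about 40 mg/dl, or twice the published figure.

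This rests on three assumptions: that the 20% is the SD of individual relative changes, that the two groups are compared without adjustment, and that the qualifying OGTT value serves as the baseline. The conclusion is not sensitive to the last: the mean baseline would have to be about 100 mg/dl for the two 20s to agree.

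What is established is an incorrect statement of detectable difference and power on the primary endpoint. A failure of the design is not established, because 16 per group is correct if 20 percentage points was intended.

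**What to change.** Keep 32 patients. State the SD and the detectable difference on one scale, and give the assumed mean baseline that links percent to mg/dl.

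- **If the 20% SD stands:** withdraw the 20 mg/dl claim. State that 16 per group gives about 80% power (78% by t-test) to detect a between-group difference of 20 percentage points in relative change from baseline to day 90, which is about 40 mg/dl at a baseline of 200 mg/dl and about 50 mg/dl at 250.
- **If an SD of about 20 mg/dl was meant:** say so and justify it, since it is no more than about 10% of an eligible baseline.

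In either case, keep the reference to baseline and day 90, add that the change is compared between groups, and report the estimated difference with a 95% confidence interval so that readers can see which effects the data exclude.

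The cost is one rewritten sentence, plus any matching text in the SAP. No patients are added and trial conduct does not change. If the 20% SD stands, the stated detectable difference becomes about twice as large.

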## Methods/Design

### Hypothesis

Vildagliptin improves glucose metabolism in patients suffering from newly diagnosed NODAT.

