### Study design and setting

This study is a prospective, single-center, double-blind, randomized, placebo-controlled, phase II trial in patients with newly diagnosed NODAT. Patient recruitment and follow-up are conducted at the Medical University of Vienna. The study recruitment has started in February 2010.

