### Safety assessments

Safety assessments will include the monitoring and recording of all adverse events (AE), including serious adverse events (SAE). An AE is any undesirable experience associated with the use of a medical product in a patient. An SAE is defined as any untoward medical occurrence that at any dose results in death, is life-threatening, requires inpatient hospitalization or prolongation of existing hospitalization, or results in persistent or significant disability/incapacity. The most probable AEs caused by vildagliptin are consistent with the known side-effects, which are the cause of the previously described exclusion criteria (table 1), such as wound healing disorders or severe renal impairment. The interruption or premature discontinuation of the study drugs might be triggered by AE, diagnostic or therapeutic procedures, abnormal laboratory values (e.g. basal ASAT/ALAT 50% elevated or more, serum creatinine 25% elevated or more) and for administrative reasons, in particular the withdrawal of the patient's consent.

**Table 1 T1:** Patients inclusion and exclusion criteria of the study.

INCLUSION CRITERIA	EXCLUSION CRITERIA
≥18 years	Patients with prior **history of type 1 or type 2 diabetes**
	
Newly diagnosed **NODAT **defined by pathologic OGTT (2 h, 75 mg glucose): glucose ≥200 mg/dL	**Body mass index **(BMI) **> 40 kg/m^2^** - **Pregnancy**
	
**Renal transplantation **(deceased or living donor) and treatment with the standard immunosuppressionat our center, consisting of a triple therapy with tacrolimusor cyclosporine A, mycophenolatemofetil, and prednisone	**Severe renal impairment **(GFR < 30 mL/min./1.73 m^2^)
	
**Stable graft function **for more than 6 months post transplant	**Severe liver impairment **(ASAT/ALAT levels over threefold elevated compared to reference values)
	
**Informed consent **of the patient	Severe blood glucose elevation with the need for **insulin therapy **or

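### Efficacy, including the primary 2 h OGTT endpoint, is analysed per protocol with ITT only as a sensitivity analysis, although the trial asks a superiority question against placebo

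*Protocol article*

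**What the plan says.** All references are to the protocol article.

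- **Analysis set (Statistical analysis plan).** Efficacy is assessed in subjects with one or more doses, on this further condition: "did not violate the protocol in a way that might affect the evaluation of the effect of the study drug(s) on the primary objective". The section then says: "The per-protocol set is employed in the analysis of efficacy variables".
- **Role of ITT (same section).** "A sensitivity analysis will be performed for efficacy with the ITT population". The Objectives section also mentions ITT, but only alongside safety outcomes.
- **Aim (Hypothesis).** "Vildagliptin improves glucose metabolism in patients suffering from newly diagnosed NODAT".
- **Design (Study design and setting; Study setting).** "This study is a prospective, single-center, double-blind, randomized, placebo-controlled, phase II trial in patients with newly diagnosed NODAT". Patients are "randomized in a 1:1 ratio into study arm A (vildagliptin) or study arm B (placebo").
- **Sample size and missing data (Statistical analysis plan).** The calculation is "Based on a two-sided testing and a standard deviation of 20% in relative changes of 2 h OGTT glucose values", with α = 0.05, β = 0.2 and 16 patients per group. Missing data are handled by LOCF.
- **Safeguards.** Medically trained staff identify major and minor deviations before study closure (Statistical analysis plan). Unblinding follows the end of the whole trial (Study intervention).
- **Stopping study drug (Safety assessments).** "The interruption or premature discontinuation of the study drugs might be triggered by AE", by procedures, by liver-enzyme or creatinine rises, or by withdrawal of consent. Risk-benefit assessment adds a stop if GFR falls below 30 mL/min/1.73 m².

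**The concern.** Randomisation makes the two arms comparable at baseline, and a test on everyone randomised inherits that protection. A set defined partly by what happens afterwards does not. If major violations are more frequent in one arm, or more frequent in patients who do badly, the per-protocol comparison mixes the drug effect with the effect of selection.

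In a non-inferiority trial a per-protocol analysis can have a claim to equal standing. Here the question is whether vildagliptin improves on placebo, and the analysis that keeps the randomised groups intact should carry the conclusion. The plan gives that analysis the secondary role. If the two disagree, the stated order lets the selected set decide. With 16 patients per arm, a few exclusions are a large share of the data.

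**Working it through.** **1. Which set governs the primary endpoint.** The primary endpoint is 2 h OGTT glucose after 3 months (Objectives; Statistical analysis plan). It is an efficacy variable, and efficacy variables are analysed per protocol. Nothing elsewhere in the article makes ITT primary for efficacy.

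**2. Whether the question is superiority.** The word is not used. The hypothesis is improvement, the control is placebo, the test is two-sided, and no non-inferiority or equivalence margin is given. Together these describe a superiority question.

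**3. The plan's own sample size.** The 16 per group reproduces if the difference and the SD are both read as 20 in the same unit, so d = 20/20 = 1:

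- n per group = 2(1.960 + 0.842)²/d² = 2 × 7.85 = 15.7, rounded up to 16.
- Power at 16 (normal approximation) = Φ(√(16/2) − 1.960) = Φ(0.868) = 0.807. With the t-test it is 0.781.

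The calculated number equals the enrolled number (2 × 16 = 32). The setting below therefore starts from 16 per arm and SD 20.

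**4. What selection could do.** The exclusion rate is not in the document, so this is an assumed worst case with a range:

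- No true effect. Changes in both arms are normal with mean 0 and SD 20, 16 per arm.
- The k least favourable changes are removed from the vildagliptin arm only.
- A two-sided t-test at 0.05 compares the remaining 16 − k with 16. There were 40,000 simulated trials per row.

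| k excluded | Bias in the difference (SD = 20) | Type I error |
|---|---|---|
| 0 | 0.0 | 5.0% |
| 1 | −2.3 | 7.2% |
| 2 | −4.4 | 10.9% |
| 3 | −6.2 | 15.4% |

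A negative bias favours vildagliptin. A repeat with a different seed and 100,000 trials gave 7.2%, 10.7% and 15.6%. When three patients were removed at random instead, the error stayed at about 5%. The damage comes from selection related to outcome, not from the smaller number.

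**5. Whether power argues for the swap.** Take d = 1 and suppose 3 of 16 vildagliptin patients get no benefit:

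- Per-protocol, those three excluded: 13 v 16, t-test power 0.73.
- ITT, all kept: mean effect 13/16 = 0.81 SD, t-test power 0.60. It is about 0.57 if the extra spread from mixing responders and non-responders is simulated.

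Power is lower under ITT in this scenario, so it does not support the swap. The reason for the swap is bias.

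**The case against.** **Stopping drug is not shown to mean exclusion.** A reader might infer that patients who stop for an adverse event, a laboratory rise or low GFR are removed from the efficacy set. The article does not say so. It excludes only major violations that bear on the primary objective, and it provides for stopping drug, so stopping is not on its face a violation. The definition of major deviations is left to the SAP, which is not shown. Some major violations may be eligibility errors already present at baseline. LOCF also suggests that some incomplete patients stay in. This objection stands: no specific route to bias, and no direction, can be read from the document.

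**The size cannot be taken from the plan.** A reader might look for an overstatement of the effect in mg/dl. That would need a discontinuation rate and a true effect in stoppers and non-stoppers, and the article gives none of these. The type I figures are a worst case and not a forecast.

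**Power.** A reader might infer that the smaller per-protocol set costs power and that this favours ITT. The comparison in the working goes the other way. A missing allowance for exclusions or non-response matters under either set and is a separate question.

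**Safeguards.** The trial is double-blind, deviations are identified before closure, unblinding comes last, and an ITT result will exist for readers to compare. These limit deliberate selection and make a discrepancy visible. They do not prevent events caused by treatment from producing violations unevenly, and they do not change which result is declared primary.

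**Conclusion.** The point holds in a limited form. The article fixes per-protocol as the main efficacy set for a superiority question, and that choice can break the randomised comparison if major violations relate to treatment or outcome. The direction and size of any bias are unknown. Under the assumed worst case, one to three exclusions from a single arm raise type I error from 5% to about 7%, 11% and 15%. If exclusions are unrelated to outcome, there is no inflation. The conclusion does not depend on treating discontinuation as a violation, nor on any power argument.

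**What to change.** 1. Make the primary efficacy analysis all randomised patients as allocated, or all randomised patients with at least one blinded dose.
2. State which of these ITT means. The Statistical analysis plan section places safety on the ITT population and also on a modified ITT set of randomised patients with at least one dose, so the ITT population for efficacy is unclear.
3. Where a month-3 OGTT was obtained after study drug was stopped, use that value in preference to LOCF. If only a baseline OGTT exists, LOCF would score the patient as unchanged, so the swap alone does not settle how early stoppers are handled.
4. Keep the per-protocol analysis as supportive.

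**Cost.** Both analyses are already planned, so swapping them is a change of wording in the protocol and SAP. Recruitment began in February 2010, so the change should be documented before unblinding. Obtaining more month-3 OGTTs from patients who have stopped would be extra work beyond wording. The estimated effect may be smaller and power lower if some treated patients get no benefit: with 1, 2 or 3 such patients among 16 at d = 1, ITT t-test power is 0.73, 0.67 or 0.60, against 0.78 with none.

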### Approval of the ethics committee and the regulatory authority

The trial is performed in accordance with the Declaration of Helsinki as well as the Austrian drug law. It subscribes to the principles outlined in the most recent version of the International Conference on Harmonization on Good Clinical. Approvals were obtained from the ethics committee of the Medical University of Vienna and the Vienna General Hospital (Reference Number 645/2009) and from the Austrian regulatory authority (Federal Office for Safety in Health Care, Austrian Agency for Health and Food Safety) and was registered to the European Clinical Trials Database (EUDRACT number: 2009-14405-14). The study has also been registered in a public clinical trial database (Identifier Number NCT00980356, http://clinicaltrial.gov).

## Discussion

### Risk-benefit assessment

We expect all patients participating in this study to benefit because of patient counseling and emphasis placed on life-style modification in both study arms. Counseling is performed according to the guidelines of the International Diabetes Federation (IDF) [4]. If the hypothesis is true, the vildagliptin group (study arm A) will experience improved glycemic control. Vildagliptin is well tolerated in patients with mild to moderate renal impairment [20]. Patients with severe renal impairment (GFR < 30 mL/min/1.73 m^2^) will not be included in our study. Patients with a GFR between 30 and 50 mL/min./1.73 m^2 ^will have weekly visits at our outpatient clinic during the first 4 weeks (serum-creatinine and ASAT/ALAT) for safety. If renal function declines for any reason to a level below 30 mL/min/1.73 m^2^, administration of the study medication will be stopped.

NODAT continues to be a common and serious metabolic complication after organ transplantation. Currently, NODAT is diagnosed and treated like T2DM, but there is only limited evidence about the efficacy and safety of the novel antidiabetic drug vildagliptin in patients with NODAT, although it is already commonly used in T2DM. Based on the differences in pathophysiology between T2DM and NODAT, the complex drug profiles in transplanted patients, and the possible influence of renal impairment on the pharmacokinetic properties of vildagliptin, the antidiabetic efficiency of this drug in NODAT remains to be established. This trial will investigate whether vildagliptin is efficient and safe in patients with NODAT.
